### Strategies to improve adherence to interventions {11c}

Not applicable as no strategies to improve adherence to interventions will be included as part of this trial.

### Relevant concomitant care permitted or prohibited during the trial {11d}

Not applicable as variability in permitted/prohibited concomitant care, to the extent that it meaningfully applies to this intervention, will not be monitored as part of this trial.

### Provisions for post-trial care {30}

Not applicable as provisions for post-trial care will be made as part of this trial.

### Outcomes {12}

Study outcome measures are shown in Table 1. Behavioural outcome data will be recorded at T1 and T3 and psychological outcome data will be recorded at T1, T2 and T3 (see Fig. 1 for full details of the schedule of assessments). The primary outcome measure is self-reported face covering behaviour recorded at 1-month follow-up (i.e. T3). The secondary outcome measures include face covering intention, attitude, subjective norms, perceived behavioural control and barrier self-efficacy (T2, T3).

**Table 1 Tab1:** Study outcome measures^1^

Domain/construct	Tool^2^	Item(s)	Description
*Primary outcome*			
Behaviour^3^ (face covering adherence) recorded at T3 (i.e. 1-month follow-up)	Self-report measure using item adapted from Fisher et al. (2020)	1	Behavioural gauge of frequency of adherence to wearing face coverings where required.
*Secondary outcomes*			
Intention^4^	Self-report Likert measure items adapted from Theory of Planned Behavior Scale Construction Guidelines reported by Ajzen (2006)	3	Statement of an individual’s motivations/ plans to engage in the target behaviour.
Attitudes^4^		3	Statement of an individual’s beliefs/ endorsement of engaging in the target behaviour.
Subjective norms^4^		1	Statement of an individual’s perceived beliefs relating to important other peoples’ views about their engagement in the target behaviour.
Perceived behavioural control^4^		3	Statement of an individual’s perceived ability to successfully engage in the target behaviour.
Barrier self-efficacy^4^	Self-report measure using items adapted from Hamilton et al. (2019)	6	Statement of an individual’s perceived ability to successfully engage in the target behaviour when faced with obstacles.

^1^Please note that study outcomes are presented following the sequence in which they will be represented in the intervention study itself

^2^All constructs will be measured at T1 (baseline), T2 (immediately post intervention) and at T3 (1-month follow-up) except behaviour which will be measured at T1 and T3 only

^3^Timeframe = the previous week

^4^Timescale = the forthcoming week

#### Behavioural measure

The complete text for the behaviour and psychological measures is included as an online supplementary resource. Self-reported face covering adherence will be measured using a single item based on previously published work [32], adapted to a UK policy/guidelines context. Participants will read the following text: ‘In the past week, when you have gone outside your home for work, grocery shopping, or other activities that involved using public transport, visiting shops/supermarkets, being in enclosed public spaces where social distancing may be difficult, or being in public spaces where you come into contact with people you do not normally meet, how often did you wear a cloth face covering that covered your nose and mouth?’. Participants will provide a response using response items ranging from ‘1’ (never) to ‘5’ (always). This measure of behaviour will be recorded at T1 and T3 only.

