#### Psychological measures

Participants will complete belief- and skill-based measures derived from two social-cognitive theories: social cognitive theory [32] and the theory of planned behaviour [33]. These theories were appropriate guiding frameworks given their centrality to behavioural science research conducted in a public health context to date [34, 35] as well as their proven validity in application to viral pandemics as a discrete public health issue [36, 37]. All constructs will be measured on multi-item scales derived based on standard psychometric guidelines [38]. All self-reported psychological measures will be gauged at T1, T2 and T3. Definitions will be provided in scales where required including definitions of ‘face coverings’ (‘In the context of the coronavirus (COVID-19) outbreak, a face covering is something which safely covers the nose and mouth. You can buy reusable or single-use face coverings. You may also use a scarf, bandana, religious garment or hand-made cloth covering but these must securely fit round the side of the face’) and ‘public spaces where this is required’ (‘on public transport; in shops and supermarkets; in enclosed public spaces where social distancing may be difficult; in public spaces where you come into contact with people you do not normally meet’).

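### The only primary-outcome item asks about a cloth face covering, narrower than the trial's own definition, so it may under-score people who wear only single-use coverings

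*Protocol article*

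**What the plan says.** Outcomes {12} makes self-reported face covering behaviour at one month (T3) the primary outcome, and Table 1 describes it as "Behavioural gauge of frequency of adherence to wearing face coverings where required". No material is named there.

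The section Behavioural measure states: "Self-reported face covering adherence will be measured using a single item based on previously published work". It then gives the text that participants will read, which ends by asking "how often did you wear a cloth face covering that covered your nose and mouth". Answers run from 1 (never) to 5 (always). On timing: "This measure of behaviour will be recorded at T1 and T3 only".

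The section Psychological measures gives the trial's definition of a face covering: something that safely covers the nose and mouth. It adds "You can buy reusable or single-use face coverings", and lists a hand-made cloth covering as one further option among several. Intervention description {11a} shows the same definition to the imagery arms. The definition is to appear in scales where it is needed; the section on the behaviour item does not say that it is shown there.

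**The concern.** The intervention promotes, and the psychological scales ask about, any face covering. The one item that decides the primary outcome credits only cloth. With a single item, nothing else in the measure can offset its wording.

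Three things are at stake. First, the type of covering worn becomes a source of variation in a score meant to measure adherence, and a real effect is diluted. Second, a participant who moves between disposable and cloth coverings from T1 to T3 registers a change in adherence that did not occur. Third, the specific objectives include mediation of effects on behaviour by attitudes, norms and self-efficacy; those predictors concern all coverings while the outcome concerns cloth only.

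**Working it through.** **Side-by-side reading.** The situations listed in the item (public transport, shops, enclosed spaces, meeting unfamiliar people) closely match the protocol's definition of public spaces where a covering is required. The mismatch therefore lies in the type of covering alone. Nothing in the protocol says that single-use coverings count as cloth, or that the definition overrides the item. The definition in fact names single-use coverings separately from cloth ones.

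**The plan's own figure.** Sample size {14}: f = 0.25, alpha 0.01, power 0.80, four groups, six covariates. With noncentrality N·f², numerator df 3 and denominator df N − 10, power is 0.7996 at N = 253 and 0.802 at N = 254. The stated 254 reproduces, and 260 gives 0.814. The wording problem does not alter this calculation; it alters the effect that will be observed.

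**Dilution.** Let s be the share in each arm who wear only non-cloth coverings and answer literally. They stay at 1 whatever they do, so an observed mean difference is (1 − s) times the true one: 0.95, 0.90 and 0.80 at s = 5%, 10% and 20%.

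**Power.** The protocol gives no s, mean, SD or T1–T3 correlation. The following are assumptions: any imagery versus control at 3:1 (195 v 65), N = 260, two-sided alpha 0.01, true effect d = 0.5. The noncentrality is d·√(195·65/260) = 6.98·d, and power without the problem is 81%.

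*(a) T1–T3 change, material use stable.* Literal exclusive non-cloth wearers score 1 at both times and contribute zero change. The difference scales by (1 − s) and the SD of change by about √(1 − s), so observed d ≈ 0.5·√(1 − s).

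*(b) T3 adjusted for T1.* Assume also a pooled mean m = 4.5, SD 0.8, a true T1–T3 correlation of 0.5 and a true adjusted d of 0.5, so the raw difference is 0.5·0.8·√0.75 = 0.346. The observed variance is V = 0.8²(1 − s) + s(1 − s)(m − 1)². The observed correlation is ρ = [0.5·0.8²(1 − s) + s(1 − s)(m − 1)²]/V = 0.745, 0.828 and 0.896. Then d = 0.346(1 − s)/√(V(1 − ρ²)).

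*(c) T3 only, unadjusted.* Same m and SD: V = 1.190, 1.679 and 2.472, and d = 0.5(1 − s)·0.8/√V.

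| s | (a) d, power | (b) d, power | (c) d, power |
|---|---|---|---|
| 5% | 0.487, 79% | 0.452, 71% | 0.348, 44% |
| 10% | 0.474, 76% | 0.430, 66% | 0.278, 26% |
| 20% | 0.447, 70% | 0.398, 57% | 0.204, 12% |

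With mean 4.0 and SD 1.0, (c) gives d of 0.405, 0.344 and 0.267 and power of about 59%, 43% and 24%.

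The mean of 4.5 must be read as pooled over arms. As a control mean it would put imagery at 4.9, where the largest SD possible on a 1–5 scale is √(0.1·3.9) = 0.62, below the assumed 0.8.

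**The case against.** The best defence is that the planned analysis absorbs much of the damage. Statistical methods {20a} treats time, including T1, as a within-participants factor, and the same item is given at T1. Someone who always wears disposables scores 1 both times, so most of the added between-person variance cancels. This stands. A reader might infer from column (c) that the wording alone wrecks the trial's power, but that column describes an unadjusted T3 comparison which the protocol does not plan. What T1 cannot restore is the diluted difference, and people who switch material add noise at a rate no document gives.

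A reader might also infer that every disposable-mask wearer scores never. That goes too far. It applies to people who wear only non-cloth coverings and answer the item as worded; mixed users fall in between, and some respondents will read cloth as any covering. The full questionnaire is in a supplement not shown, so a definition displayed near the item cannot be excluded, although the item text itself is presented as what participants read.

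A third tempting reading is that the bias differs by arm, for example that process imagery leads people to carry spare disposables and so lowers their score. The protocol asks only for strategies and mentions no spares; participants could as easily plan to carry a reusable covering. Differential bias is possible but nothing in the protocol supports it.

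**Conclusion.** The mismatch holds on the face of the protocol: the sole primary-outcome item is narrower than the construct in Table 1 and the trial's own definition, and no section reconciles them. Its direction is to under-count adherence among literal, exclusive wearers of non-cloth coverings and to shrink any true mean difference to (1 − s) of its value, assuming s is the same in each arm.

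The size cannot be fixed from the protocol because s is not given. Under the stated assumptions and s from 5% to 20%, power falls from 81% to between 79% and 70% in a change analysis with stable material use, and to between 71% and 57% with T1 as a covariate. This is a moderate validity problem with a cheap remedy. It does not invalidate the trial, but a null result could not be read simply as failure of the imagery exercises.

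**What to change.** **For any further use of the instrument:** delete the word cloth from the behaviour item at both T1 and T3, and display the definition from Psychological measures with it. The cost is one word, one displayed definition and a small departure from the source item, which the protocol already says is adapted to the UK context.

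**For data already collected** (Trial status gives the end of enrolment as 28 February 2021, so rewording cannot help these responses):
- report the exact wording of the item;
- state that the outcome may under-count wearers of single-use coverings, and so is not a clean measure of adherence to the legal requirement;
- keep T1 behaviour in the primary analysis, as planned;
- interpret a null result with that limitation in view.

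Relabelling the outcome outright as cloth-covering use would overcorrect, because it is unknown how many respondents read the item literally. The reporting steps cost a few sentences.

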#### Psychological measures

Participants will complete belief- and skill-based measures derived from two social-cognitive theories: social cognitive theory [32] and the theory of planned behaviour [33]. These theories were appropriate guiding frameworks given their centrality to behavioural science research conducted in a public health context to date [34, 35] as well as their proven validity in application to viral pandemics as a discrete public health issue [36, 37]. All constructs will be measured on multi-item scales derived based on standard psychometric guidelines [38]. All self-reported psychological measures will be gauged at T1, T2 and T3. Definitions will be provided in scales where required including definitions of ‘face coverings’ (‘In the context of the coronavirus (COVID-19) outbreak, a face covering is something which safely covers the nose and mouth. You can buy reusable or single-use face coverings. You may also use a scarf, bandana, religious garment or hand-made cloth covering but these must securely fit round the side of the face’) and ‘public spaces where this is required’ (‘on public transport; in shops and supermarkets; in enclosed public spaces where social distancing may be difficult; in public spaces where you come into contact with people you do not normally meet’).

##### Intention

Intention to wear face coverings where required will be measured by presenting participants with the stem ‘Over the next week, wearing a face covering while in public spaces where this is required is something...’ followed by three items (e.g. I intend to do). Answers will be provided using response items ranging from ‘1’ (strongly disagree) to ‘5’ (strongly agree).

##### Attitudes

Attitude towards face covering behaviour will be measured by presenting participants with the stem ‘Wearing a face covering while in public spaces where this is required over the next week is something…’ followed by three pairs of response anchors (e.g. ranging from ‘1’ (not worthwhile) to ‘5’ (worthwhile)).

##### Subjective norms

Subjective norms will be measured using four items in total. This scale will comprise two injunctive norm items (e.g. ‘Most people who are important to me (e.g. friends, family) would want me to wear a face covering while in public spaces where this is required over the next week’); and two descriptive norm items (e.g. ‘Most people who are important to me (e.g. friends, family) will be wearing a face covering while in public spaces where this is required over the next week’). Answers will be provided using response items ranging from ‘1’ (strongly disagree) to ‘5’ (strongly agree).

##### Perceived behavioural control

Perceived behavioural control (PBC) towards face covering behaviour will be measured by three items in total. For one item, participants with the stem ‘How much personal control do you think you have in wearing a face covering while in public spaces where this is required over the next week’ (1 = no control at all, 5 = complete control). For two further items, participants will read a stem statement ‘For me to wear a face covering while in public spaces where this is required over the next week is’ followed by two response options (e.g. ranging from ‘1’ (impossible) to ‘5’ (possible)).

##### Barrier self-efficacy

Barrier self-efficacy towards face covering behaviour will be adapted from a 6-item scale reported in previous work [39] and in line with self-efficacy scale construction guidelines [40]. Participants will respond to the stem ‘Rate your degree of confidence in wearing a face covering while in public spaces where this is required under the following conditions’ followed by six response items (e.g. ‘When I feel stressed/frustrated’; ‘When accessing my face covering is difficult’) and using response options ranging from ‘1’ (cannot do at all) to ‘5’ (highly certain can do’).

#### Personality traits

Personality trait measures will be taken at T1 and examined as moderators of intervention effects. Preceding all personality items, participants will read the stem ‘Describe yourself as you generally are now, not as you wish to be in the future. Describe yourself as you honestly see yourself, in relation to other people you know of the same sex as you are, and roughly your same age’. Participants will then complete scale-specific items as described below.

##### Conscientiousness

Conscientiousness will be measured using a validated scale [20]. Participants will read a further stem ‘Typically, I:’, after which they will provide responses to ten items (e.g. ‘Am always prepared’) including four reverse scored items (e.g. ‘Make a mess of things’). Answers will be provided using response items ranging from ‘1’ (very inaccurate of me) to ‘5’ (very accurate of me).

##### Narcissism

Narcissism will be measured using a scale previously reported elsewhere [22]. Participants will provide responses to 16 items (e.g. ‘People always seem to recognize my authority’). Answers will be provided using response items ranging from ‘1’ (very untrue of me) to ‘5’ (very true of me).

##### Light triad personality traits

Light triads personality traits will be measured using scale reported previously [21]. Participants will complete 12 items in total (4 per trait) relating to Faith in humanity (e.g. ‘I think people are mostly good’); to Kantianism (e.g. ‘I prefer honesty over charm’) and to Humanism (e.g. ‘I tend to treat others as valuable’). Answers will be provided using response items ranging from ‘1’ (very inaccurate of me) to ‘5’ (very accurate of me).

#### Covariates

All covariates will be measured at T1 and T3 only.

##### Demographic measures and COVID-19 related activity

Demographic measures will be collected at T1 including: (i) sex (0=male, 1=female, free text box for other sex); (ii) age (recorded in years); (iii) ethnicity (free text box for self-identified ethnicity); and (iv) occupation (free text box for occupation-related information). An additional measure will be included to approximate time spent in public spaces where COVID-19 protective behaviours would be required by UK law. This measure will consist of three items (e.g. I use public transport on a daily basis). Answers to this measure will be provided at T1 and T3 using response items ranging from ‘1’ (very inaccurate of me) to ‘5’ (very accurate of me).

##### Imagery ability

Dispositional differences in Imagery ability will be measured using an ‘imagery fidelity’ measure described elsewhere [41]. Participants will read the stem statement: ‘When I think about wearing a face covering while in public spaces where this is required over the next week the imagery around this that occurs to me is:’ and will then provide responses using four response items ranging from ‘1’ (not clear) to ‘5’ (clear).

#### Data quality

Three questions will be included in the T1 survey to identify cases of extreme inattentive responding. Evidence has suggested that inattentive responding holds diverse negative implications for data quality (e.g. experimental manipulations, statistical power) and can serve to mask intervention effects. Screening out unambiguously inattentive participant responses may therefore serve to mitigate reduced power and effect size estimation [42, 43]. These items will be set up so that a correct response would only be possible following careful reading of the item (e.g. ‘please choose option four to ensure you are paying attention’). Participants who provided an incorrect response to *all* three items will be excluded from the final dataset. These items will be included as a crude metric for demonstrating protocol adherence (i.e. evidence of a reasonable level of engagement with survey completion) and as a way of identifying where clear non-engagement with the survey is apparent (e.g. the incorrect option chosen for all three responses).

To further maximize data quality, we will omit responses where there is negligible evidence of engagement in the mental imagery exercise (i.e. screened free-text responses that contain unclear/irrelevant or indifferent responses will be excluded from analysis).

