### Sample size {14}

#### Statistical power and sample size

An a priori power analysis has been conducted using G*Power V.3.1 for an ANCOVA model estimating fixed effects, main effects and interactions [44]. A medium effect size (*f*=0.25) with power set to 0.80 and alpha set to 0.01 (adjusted given multiple tests and therefore to control for type I error rate inflation) will be sought. Inclusion of six covariates (gender; age; ethnicity; occupation; approximate time spent in places where wearing face coverings would be mandatory; imagery ability) was specified. Power analysis indicated that a minimum sample size of 254 will be required. In developing the recruitment strategy, it is important to be mindful of introducing attrition bias, i.e. bias created by retaining participants with particular characteristics in a way that alters the complexion of the sample. Guidance on acceptable attrition levels has indicated that > 20% study attrition increases the risk of attrition causing serious threats to study validity [45] though debate surrounds precisely when attrition bias may most threaten study validity (e.g. [46, 47]). The study aim is, therefore, to recruit 312 individuals at baseline/T1 to meet a required sample size of 260 at follow-up/T3 (i.e. allowing for no more than 20% attrition).

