## Assignment of interventions: allocation

### Sequence generation {16a}

After participants have completed complete demographic, psychological and behavioural measures at baseline (T1) they will be randomized to the outcome imagery exercise, the process imagery exercise, a combined condition (comprising the outcome and process imagery exercises) or a control condition. The allocation ratio (i.e. the ratio of participant numbers in each of the conditions) is intended to be equal across groups (i.e. 1:1:1:1). Throughout the recruitment period, the protocol author will conduct biweekly checks to audit that roughly equal allocation of participants to conditions has occurred. Randomization will be conducted via a Qualtrics randomizer features embedded in the T1 survey. The Qualtrics randomizer uses a Mersenne Twister pseudorandom number generator approach which is a widely used approach employed within standard statistical packages (e.g. IBM SPSS, Microsoft Excel). This approach follows a random method by which the randomization sequence cannot be determined until participant assignment has occurred while ensuring roughly even distribution of participants across groups. The researcher team will be blind to group assignment at the point of randomization.

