## Data collection and management

### Plans for assessment and collection of outcomes {18a}

#### Data collection and management

Participant names will not be included in the dataset and each participant will be assigned a study ID. All data will be downloaded in secure form to institutional cloud services (i.e. OneDrive). All data will be backed-up securely and all data files will be securely password protected and encrypted. Throughout project activities, data files and printed materials that are no longer required will be destroyed. Email address data will be stored in a separate document in an encrypted folder and will be destroyed once recruitment is completed. Range and consistency checks will be conducted on all questionnaire data promptly by the research team. Because questionnaire data will be collected using a ‘Force Response’ setting on Qualtrics there will be no missing data for this study. To address incomplete participant responses we will conduct an intention-to-treat (ITT) analysis in addition to the complete case analysis. ITT is an assessment of all trial participants in analysis regardless of whether or not they provided incomplete responses or failed to provide follow-up responses and provides a way of producing an unbiased estimate of intervention efficacy of the intervention in respect of study adherence [48].

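### Attention-check failures are, on the natural reading, randomised and then removed, which conflicts with the promised ITT analysis of all participants

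*Protocol article*

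**What the plan says.** All places are in the protocol article.

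- **Data quality (under Outcomes {12}).** "Three questions will be included in the T1 survey to identify cases of extreme inattentive responding". Those who get all "three items will be excluded from the final dataset". The section also gives the purpose: "These items will be included as a crude metric for demonstrating protocol adherence".
- **Sequence generation {16a}.** "After participants have completed complete demographic, psychological and behavioural measures at baseline (T1) they will be randomized", and "Randomization will be conducted via a Qualtrics randomizer features embedded in the T1 survey". No step between the baseline measures and the randomiser turns anyone away.
- **Eligibility criteria {10}.** The list covers residence, questionnaire completion, engagement with the imagery exercise, exposure to indoor public places, and consent. The attention items are not on it.
- **Data collection and management (under {18a}).** An ITT analysis is promised alongside the complete-case analysis, and "ITT is an assessment of all trial participants in analysis regardless of whether or not they provided incomplete responses".
- **Sample size {14}.** The minimum is 254. The plan is to recruit 312 at T1 "to meet a required sample size of 260 at follow-up/T3", with attrition as the only stated allowance.
- **Goals and objectives (under Objectives {7}).** T1 is defined as the baseline assessment before randomisation.

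**The concern.** The article gives two rules about who is analysed. One takes attention-check failures out of the data file itself, so read literally no analysis can contain them. The other says the ITT analysis covers every participant. If failures have been randomised, both cannot hold. The article does not say which prevails: the section on non-adherence and missing data {20c} only points to {20a}, which has no rule on either.

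The stated purpose sharpens the conflict. Removing people because a marker shows poor adherence is per-protocol reasoning, and ITT exists to avoid it. At stake is whether the analysis labelled ITT is one. There is a smaller cost in numbers, because the recruitment target allows for attrition but not for these removals.

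**Working it through.** **1. Are failures randomised?** The items and the randomiser share one survey. No gate is described, the checks are not eligibility criteria, and the rule acts on the final data file. The natural reading is that failures pass through the randomiser and are removed later. This is an inference; no sentence states it.

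**2. Does the order of items and randomiser matter?** The order is not stated.

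- *All three before the randomiser.* The definition of T1 points this way. Failure is then a baseline characteristic and cannot depend on arm. Removal narrows the population and breaks the ITT definition, but does not by itself bias the comparison.
- *Any after the randomiser.* What a participant has gone through by then differs by arm, from viewing one image (control) to 15–25 minutes of exercises (combined). Failure could then depend on arm. Because exclusion needs all three answers wrong, anyone who gets an earlier item right can never be removed, which limits the dependence unless all three items come late.

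**3. The plan's own sample size.** Inputs from Sample size {14}: f = 0.25, alpha 0.01, power 0.80, six covariates. Sequence generation {16a} gives four equal groups. The numerator df is not stated; 3 is assumed because it reproduces the plan's figure.

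Noncentral F, with λ = N·f² and df2 = N − 4 − 6:

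- N = 254: λ = 254 × 0.0625 = 15.875, df2 = 244, power 0.802. The smallest N reaching 0.80 is 254, as stated.
- N = 260: λ = 16.25, df2 = 250, power 0.814.
- Margin: 260 − 254 = 6 people; 6/260 = 2.3%.

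**4. Effect of the removals.** The failure rate e is not in the document; 2% and 5% are assumptions.

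| e | Removed from 312 (312·e) | Left of 260 (260·(1−e)) | Power | Starters for 312 passers (312/(1−e), rounded up) |
|---|---|---|---|---|
| 0 | 0 | 260 | 0.814 | 312 |
| 2% | 6.2 | 254.8 | about 0.80 | 319 |
| 5% | 15.6 | 247 | 0.786 | 329 |

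For a one-df factorial main effect, power is 0.923 at 260 and 0.908 at 247.

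**5. A less favourable case.** 312 is 260 × 1.2, which absorbs 1 − 260/312 = 16.7% attrition. At a true 20%, 312 × 0.8 = 249.6 remain before any attention-check removal (power about 0.79). Failure rates of 1%, 5% and 10% on top leave about 247, 237 and 224, with power 0.786, 0.763 and 0.730. The first part of that shortfall comes from the inflation step and is a separate matter.

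**6. Against the reported numbers.** Trial status gives 297 with complete T1 and T3 data. If that count precedes exclusions (not stated), removals would have to exceed (297 − 254)/297 = 14.5% to fall below 254.

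**The case against.** The strongest reply is that this is an ambiguity about a mild rule. T1 is defined as preceding randomisation, so the attention items most naturally sit among the baseline measures. The section itself speaks of screening out, and the schedule figure and supplementary questionnaire, which are not shown, may fix the order. Analysis sets are often defined in a full protocol or SAP, and the ITT sentence on its face includes everyone. The power effect is trivial, and 297 completers makes a shortfall unlikely.

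Much of this stands. A reader might infer that the document says failures are randomised and then deleted; it does not, and the order is open. A reader might also infer removal linked to arm through fatigue. That needs items after the randomiser, which the definition of T1 makes unlikely, and needs all three answers wrong. Nor is it settled that the ITT set omits these people: that is one way of resolving the conflict, and the other makes the Data quality rule untrue.

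The reply does not remove the conflict. Leaving the definition of analysis sets to a SAP would be no fault, but here the article states two rules that cannot both hold for anyone who was randomised and failed all three items.

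**Conclusion.** The point holds as an unresolved conflict about the analysis population, resting on the inference that failures are randomised. If the items precede the randomiser, the harm is a broken ITT definition and a few lost participants, without bias in the arm comparison from this rule alone. If any follow it, removal could depend on arm.

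The numerical effect is small: from 0.81 to about 0.79 at an assumed 5% failure rate among 260 completers, with df1 = 3. The document gives no failure rate and does not say whether 260 is counted before or after exclusions, so a missed power target is not shown.

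It would also be wrong to infer that settling the attention checks yields a clean ITT set. Eligibility criteria {10} and Data quality also drop people whose free text shows too little engagement with the imagery exercise. The control arm has no such exercise, so that rule can act only in the three imagery arms. It is the more serious post-randomisation exclusion and would remain.

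**What to change.** **For the design as planned, or a repeat.** Place all three attention items before the Qualtrics randomiser and end the survey there for anyone who fails all three, so that failures are never randomised. Drop the later removal from the final data file, and state in Sample size {14} that 312 and 260 count people who passed. This costs one survey branch, a sentence in each of the two sections, and a few more starters: 319 to 329 instead of 312 at an assumed 2–5% failure.

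**For the data already collected.** Trial status says enrolment ended on 28 February 2021, so the change must be made in the analysis. Keep all randomised participants in the ITT analysis whatever their attention-check result. Apply the exclusion only in the complete-case analysis or a sensitivity analysis. State where the items sat relative to the randomiser, and report the number removed by arm. This costs a few sentences and one small table.

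**In both cases.** Keep the free-text engagement exclusion out of the ITT analysis as well, and reconcile the Data quality and Eligibility criteria sections with the ITT definition.
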